## Results

Results from the RCT will be analyzed in spring 2024, published in peer-reviewed journals in the fields of palliative care and telepalliation, and presented at relevant international conferences by fall 2024.

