**Results:**

The collection of data began in May 2021 and will be completed in August 2024. The results of the study will be published in peer-reviewed journals and presented at international conferences. Results from the telepalliation program are expected to be published by fall 2024.

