## Methods

### Research Design

The telepalliation program will be conducted as a multimethod RCT using qualitative and quantitative data collection techniques [12,13]. The intervention group will take part in the telepalliation program, while the control group will follow a traditional palliation program at Southwest Jutland Hospital, Esbjerg, Denmark. Enrollment of patients began in May 2021, and the RCT will end in August 2024. The study will be reported following the SQUIRE (Standards for Quality Improvement Reporting Excellence) guidelines [14].

The purpose of the telepalliation study is to test, implement, and evaluate a telepalliation program for patients receiving SPC at the Hospital of Southwest Jutland, Esbjerg, Denmark. To accomplish this goal, we combine clinical, psychosocial, interorganizational, and health economic approaches. This will be done by collecting data on symptom scores over time, patients scoring their feeling of security over time, and interviews with patients, their families, HCPs of the specialist team, and primary HCPs. Interviews will focus on the use of the TelePal platform but also on the interorganizational perspective of the communication between primary and secondary health systems. Evaluation of overall economic implications will be done separately at the end of the study. The telepalliation study will be implemented and evaluated in an RCT.

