### Details on the RCT

The randomization is performed randomly by a digital tool. The randomization was designed as a block with equal numbers for the intervention and control groups. Only 1 person was blinded. The intervention group participated in the telepalliation program, and the control group received standard SPC [1,3] that was individualized for each patient.

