### Ethical Considerations

This study was approved by the ethical committee in Northern Jutland (N-202000094) and registered at ClinicalTrials.gov (NCT04995848). This study will be conducted according to the Declaration of Helsinki. Patients in palliative care and their relatives are a vulnerable group and will be informed thoroughly about the purpose of the study. Accordingly, it is specified that the patient can withdraw their consent at any given time in the study without having any consequences for their treatment. Individuals will be considered as participants in the trial, whereas their relatives will not be considered as participants. However, they are invited to voluntarily participate in the use of the digital platform TelePal. To clarify and ensure that all relatives are fully informed about the study and feel safe about their participation, a written letter of information was sent to all relatives. Patients are enrolled in the study for a maximum of 6 months or until (1) they stop being followed by the palliative team due to lack of symptoms or (2) they are diagnosed with delirium based upon the Confusion Assessment Method score [22,23]. Patients who develop cognitive impairment will be dismissed from the study, and patients who develop delirium will also be dismissed, and data collection will end immediately.

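### The article dates the RCT analysis to spring 2024 but the end of data collection and of the trial to August 2024; the dates need reconciling so that the comparison by arm follows complete follow-up.

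*Protocol article*

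**What the plan says.** Three places in the protocol article give dates.

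- Abstract, Results: "The collection of data began in May 2021 and will be completed in August 2024".
- Methods, Research Design: "Enrollment of patients began in May 2021, and the RCT will end in August 2024".
- Results section: "Results from the RCT will be analyzed in spring 2024", with journal publication and conference presentation to follow by fall 2024. The Abstract gives the same publication target: "Results from the telepalliation program are expected to be published by fall 2024".

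Four other statements bear on the point. Table 1 has quality of life, the primary outcome, measured every week. Ethical Considerations sets the length of follow-up: "Patients are enrolled in the study for a maximum of 6 months or until" one of two listed events occurs. Details on the RCT says "Only 1 person was blinded", without giving that person's role. Table 1 places the platform-use and cost analyses at the end of the project.

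The Statistical Analysis section describes no interim comparison and no early data cut-off.

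**The concern.** The analysis is dated before the data are complete. The conflict is within current text, and the obvious ways of reconciling the dates do not work. The spring sentence concerns the RCT results, so it cannot be confined to the interviews. Research Design says that the trial itself ends in August, so the later date cannot be confined to qualitative or cost follow-up.

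Two things are at stake. First, an analysis at the stated time would omit the last part of follow-up on the primary outcome and lose some precision. Second, a comparison by arm would exist while patients who mostly know their allocation are still rating their own quality of life, pain and sense of security. A trial with self-reported outcomes and little blinding is better off without that exposure, and avoiding it costs little.

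**Working it through.** **1. The dates side by side**

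| Event | Date | Place |
|---|---|---|
| Start of enrolment and data collection | May 2021 | Abstract; Research Design |
| Analysis of the RCT | Spring 2024 | Results |
| End of data collection and of the RCT | August 2024 | Abstract; Research Design |
| Publication | By fall 2024 | Abstract; Results |

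**2. How early is spring 2024?** Take spring as 1 March to 31 May. From May 2021 that is month 34 to month 37. May 2021 to August 2024 is 39 to 40 months, depending on the days chosen.

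- Fraction elapsed: 34/40 = 0.85 to 37/39 = 0.95.
- Time remaining: 39 − 37 = 2 months to 40 − 34 = 6 months.

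**3. Whose follow-up is cut?** With up to 6 months per patient, a cut-off on 1 March affects patients enrolled after about 1 September 2023, and a cut-off on 31 May affects those enrolled after about 30 November 2023. This holds even if enrolment had closed by about February 2024, which is 6 months before August. Patients who had already left the study would lose nothing.

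**4. The plan's own sample size.** Inputs from Sample Size: means 59.5 and 68.43 (difference 8.93), SD 20.5, power 80%, and a 95% CI, read as two-sided alpha 0.05.

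n per arm = 2 × (1.96 + 0.8416)² × 20.5² / 8.93² = 82.7, so 83 (84 with the t distribution).

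The stated figure, read as 91 per arm, is not reproduced. An allowance of about 8% for dropout would give it (83/0.92 = 90.2, so 91), but the article states none. The difference is on the safe side and does not affect this point. I use 91, as stated.

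**5. Power at the stated analysis time.** Power = Φ(8.93 / (20.5 × √(2/n)) − 1.96). Assume that information accrues evenly over calendar time, so n = 91 × fraction elapsed.

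| Fraction | n per arm | Power |
|---|---|---|
| 1.00 | 91 | Φ(2.938 − 1.96) = 83.6% |
| 0.95 | about 86 | Φ(2.864 − 1.96) = 81.7% |
| 0.85 | about 77 | Φ(2.709 − 1.96) = 77.3% |

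This treats the missing follow-up as missing patients, which is a simplification.

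**6. Type I error, only if the test were done twice.** For two looks, each at |Z| > 1.96 and with correlation √f, the overall error is 1 − P(|Z₁| < 1.96 and |Z₂| < 1.96). It is 0.068 at f = 0.85 and 0.060 at f = 0.95. The article describes one analysis, so this calculation does not describe the plan as written.

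**The case against.** The strongest answer is that this is a timetable slip and not a design decision. The spring date stands in one sentence that also covers publication and conferences. It is not a cut-off or stopping rule, and neither Statistical Analysis nor Details on the RCT mentions an early comparison. That is a fair reading, and the article cannot rule it out. It cannot confirm it either: the target of publication by fall 2024 fits a spring analysis more easily than one begun after August.

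The loss is also modest. Six months is a maximum, and the Introduction stresses how short the time from referral to death can be, so many recent enrollees may already have finished by spring. If enrolment closed around February 2024, every patient would be in the data set and only some late questionnaires would be missing. Both points stand, and they make the power figures a rough guide.

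Three stronger readings are tempting but lack support:

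- **The type I error is inflated.** A reader might infer an undeclared first look to be repeated in August. The article mentions no second test. One analysis at 5%, at a time fixed by the calendar, does not inflate the error even if it is early.
- **The recruiting and treating team would hold the comparative results.** The article does not say who would see them. The one blinded person has no stated role and could be the analyst.
- **Recruitment would be influenced.** If follow-up of up to 6 months is to finish in August, little or no recruitment would remain by spring.

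**Conclusion.** The contradiction is real and certain: the article dates the analysis before the end of the data to be analysed. Followed literally, it would omit about 2 to 6 months of collection. Power for the stated effect would be about 77-82% against 83.6%, assuming 91 per arm, even accrual, and a loss that acts like fewer patients. The comparison would also be made while largely unblinded patients were still reporting.

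Whether an early analysis was intended cannot be told from the article. An overall error of about 6-7% would apply only if an early comparison was in fact made and will be repeated. Severity is moderate to minor: the point is more than clerical, because it fixes when the primary comparison is made, but its likely numerical effect is small.

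**What to change.** Bring the Results section into line with the Abstract and Research Design. Suggested text: *The comparison by arm will be made once, after the last patient's follow-up is complete (August 2024) and the data are final.* Move the publication and presentation dates in the Results section and the Abstract to match.

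If a comparison by arm was made earlier and will be repeated, report it as an interim look and adjust the level of the final test for the fraction of information then available. If there was none, no adjustment is needed.

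The cost is a change of text and a delay of a few months in publication. The sample size does not change.

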## Discussion

### Principal Findings

The aim of the telepalliation study is to test, implement, and evaluate the telepalliation program for patients receiving palliative care. The study is carried out using combined clinical, psychosocial, interorganizational, and health economic approaches.

A scoping review by Steindal et al [36] has shown that the use of telehealth in palliative homecare improves access to HCPs at home and enhances patients’ sense of security and safety. The review indicated that there are contradicting results as to whether the use of telehealth will improve burdensome symptoms and QoL [36]. A study by Caraceni et al [11] has shown that telemedicine facilitates patient-clinician interaction, but the investigation of clinical impact should be better documented.

The TelePal platform and program have been developed in a participatory design process, and an important part of the study is to explore how patients in palliative care and their relatives experience the TelePal program and use the digital platform. Important questions to explore are whether the patients have the resources to use the technology, and if so, what functions are they and their relatives using and what value do they attribute to these functions. Another important question revolves around the ethical issues of using a digital platform in the collaboration between patients in palliative care and HCPs. Steindal et al [36] stated that there is a need for increased knowledge about these issues. We hope that the platform can help increase the feeling of security for the patients and relatives and ease communication, collaboration, and coordination among the HCPs across sectors.

In palliative settings, video has been used for conferences between patient’s homes and between rural health professionals and specialist centers to support patients and their relatives at home [8]. The use of video can increase the collaboration between SPCTs and GPs [6] and fit the practice of home-based palliative care, thus resulting in a more empathetic patient-professional relationship [37]. In the TelePal study, we will explore how the platform will affect the patient care process and interorganizational collaboration among the HCPs across sectors. We have not identified other studies using a telepalliation platform and a program.

What are the health economy costs of running a telepalliation program? Caraceni et al [11] highlighted the lack of cost-effectiveness studies within telepalliation. In the TelePal study, we will conduct a cost-effectiveness evaluation to show that it will be cost-effective, reduce the cost for transportation, and reduce patients’ travel to the hospitals.

### Limitations

A limitation of this study is that it is a 1-center study and therefore reflects the findings of only a single SPCT. The fact that it has been conducted only in Denmark means that it reflects findings within a Danish context. These findings may not necessarily be applicable to other settings and in different contexts.

### Conclusions

The expected outcomes are increased QoL and increased sense of security for patients in the intervention group. We expect that the study will have a clinical impact on future telepalliation for patients who are referred to a palliative team.

## Abbreviations

AAU: Aalborg University
EORTC QLQ-C15-PAL: European Organisation for Research and Treatment of Cancer Quality of Life Questionnaire Core 15 Palliative Care
GP: general practitioner
HCP: health care professional
QALY: quality-adjusted life year
QoL: quality of life
RCT: randomized controlled trial
SPC: specialized palliative care
SPCT: specialized palliative care team
SQUIRE: Standards for Quality Improvement Reporting Excellence
